**Fig. 2 Fig2:**
[figure not shown]
Mock data for changes in aerobic fitness. The blue shaded areas indicate the holiday periods. The black dots are measured values; the white dots are estimated fitness levels when extrapolated to the start, or back-extrapolated to the end of the holiday periods

Time use will be quantified as 24-h activity compositions [61]. These activity compositions will consist of mutually exclusive and exhaustive parts of the day which together sum up to 24 h. Accelerometry compositions will capture daily times spent in energy expenditure bands (sleep, sitting, light, moderate and vigorous PA), and MARCA compositions will capture times spent in activity “types” (e.g. chores, physical activity, school). The average daily accelerometry and MARCA time-use compositions will be used for analyses. Compositions will be expressed as isometric log ratios [62] to enable their inclusion in the linear mixed effects models. Differences in rates of change in outcome variables (S–H) will be regressed against differences between the in-school composition (C_S_) and the holiday composition (C_H_) (C_S–H_) to test Hypothesis 3 (∆_S–H_ is correlated with C_S–H_). Compositional isotemporal substitution analysis [63] will be used to quantify the change in fitness and fatness when replacing a given quantum of one component of the activity composition (e.g. 30 min of sitting) with the same quantum of another (e.g. 30 min of moderate- to vigorous- intensity physical activity), while holding the remaining components constant. A similar analysis will be performed for diet, with macronutrient mix or food group intake as the composition, and total energy intake as a covariate. Analyses will adjust for age, sex, SEP, parenting style, weight status, and pubertal status, where appropriate.

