### Measures

The schedule of assessments across the study period is shown in Fig. 1. Diet and time use (accelerometry and 24-h recall) assessments will be conducted at the beginning (Term 1) and end (Term 4) of each school year and during each summer holiday period (December/January) for study years 1 and 2. Anthropometric and fitness measures will be taken at the beginning and end of each school year. Trained research personnel will administer fitness and fatness assessments in school, during usual school hours.

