Specific types of activity will be captured using the Multimedia Activity Recall for Children and Adults (MARCA), a computerised 24-h recall [29]. Participating children will recall every activity (e.g. sports, reading, household chores) they did over a 2-day period during 30-min face-to-face interviews (terms 1 and 4) and during computer-assisted telephone interview (summer holidays). This will be done using a segmented-day format with a resolution of 5 min or more. Participants will choose from 500 activities, yielding a high-resolution snapshot of how they used their time. The MARCA has evidence of good validity (r = 0.4–0.7) when compared against accelerometry [29], pedometry [30] and doubly-labelled water [31], and excellent test-rest reliability (ICC = 0.88–1.00) [29]. Each activity is linked to a compendium of energy expenditures [32] so that overall and activity-specific energy costs can be estimated. Where possible, the same two days will be recalled at each time-point, including at least one weekday and one weekend day, overlapping where possible with GENEActiv data.

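### The MARCA composition counts school as a part, but school time is zero by definition in the summer holidays, so its log ratios and the MARCA term-minus-holiday difference are undefined as written

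*Protocol article*

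**What the plan says.** The relevant text is in the protocol article, Methods/design, Analysis, in the time-use paragraph that follows Fig. 2. It fixes four things.

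- A time-use composition consists of "mutually exclusive and exhaustive parts of the day which together sum up to 24 h".
- For the recall instrument, "MARCA compositions will capture times spent in activity “types” (e.g. chores, physical activity, school", so school is named as one of the parts.
- "Compositions will be expressed as isometric log ratios [62] to enable their inclusion in the linear mixed effects models".
- Hypothesis 3 regresses the term-minus-holiday difference in rates of change on "differences between the in-school composition (C_S_) and the holiday composition (C_H"). Isotemporal substitution follows on the compositions.

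The same paragraph states that "The average daily accelerometry and MARCA time-use compositions will be used for analyses".

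The instrument is used in both periods. Under Time use, the recall is done face to face in Terms 1 and 4 and "during computer-assisted telephone interview (summer holidays"). Under Measures, diet and time use are assessed "during each summer holiday period (December/January) for study years 1 and 2". Each occasion covers two recalled days, where possible with at least one weekday and one weekend day.

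For diet, the Analysis section proposes a similar analysis "with macronutrient mix or food group intake as the composition".

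**The concern.** An isometric log ratio takes the logarithm of every part, so every part must be positive. School time can be positive on the term side, when a school weekday is recalled. In the summer holidays it is zero for essentially every child. This is a structural zero: the activity is unavailable, and no finer or longer recall would make it positive. A named part, the chosen transformation and the chosen contrast therefore cannot hold together.

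At stake is the activity-type half of the time-use analysis in Hypothesis 3. An analyst following the text gets infinite coordinates on the holiday side and must then improvise. Regrouping parts or choosing a replacement value after the data are in is an avoidable degree of freedom.

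**Working it through.** The article gives no figure to reproduce. The check asks whether the coordinates exist, and what a replacement value would do. All minutes below are assumptions, because the article gives none.

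**Formula.** For D parts with school first, the school coordinate is z = √((D−1)/D) × ln(school / geometric mean of the other parts). With six parts the factor is √(5/6) = 0.9129.

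**1. As written.** Take a term day of 200 min school and 560, 120, 200, 100 and 260 min in the other parts (sum 1440). Take a holiday day of 0 min school and 600, 140, 260, 120 and 320 min (sum 1440).

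- The geometric means of the other parts are 203.55 (term) and 242.50 (holiday).
- Term: z = 0.9129 × ln(200/203.55) = −0.016.
- Holiday: z = 0.9129 × ln(0/242.50) = −∞, so the difference is +∞.
- If school is placed last in the ordering, all five holiday coordinates are infinite. Reordering the parts does not help.

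**2. Small-value replacement, level of the difference.** Replace the zero by ε and compute −0.016 − 0.9129 × ln(ε/242.50):

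| ε (min) | School coordinate of the difference |
|---|---|
| 0.5 | 5.63 |
| 1 | 5.00 |
| 2 | 4.36 |
| 5 | 3.53 |
| 10 | 2.89 |

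The whole range is 0.9129 × ln(10/0.5) = 2.73, which comes from the constant alone.

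**3. Effect on the regression when all zeros are alike.** Child i's school coordinate of the difference is a_i − 0.9129 × ln ε, where a_i contains only term school time and the other parts. With one ε for everybody, the second term is the same for every child and goes into the intercept. The slopes do not change. Simulated six-part days for 300 children confirmed this: the slopes and the residual sum of squares were identical for all five constants, and only the intercept moved. By the same expression, a_i holds no information on holiday school time.

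**4. Substitution involving school.** Move 30 min from sleep to school in the holiday day, so that sleep goes from 600 to 570. The school coordinate changes by 0.9129 × [ln((ε+30)/ε) − (1/5) ln(570/600)].

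- ε = 0.5: 0.9129 × (4.111 + 0.010) = 3.76.
- ε = 10: 0.9129 × (1.386 + 0.010) = 1.27.

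This is a threefold range from the choice of constant. Taking 30 min out of school on that day is impossible.

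**5. When zeros are not uniform.** Suppose a few children report 60 min of a school-type activity in the holidays. With the other parts equal, they stand apart from the rest by 0.9129 × ln(60/ε): 4.37 at ε = 0.5 and 1.64 at ε = 10. That is a high-leverage split whose width is set by ε. In one illustrative simulation the school slope was 0.42 with uniform zeros. With 5% of children at 60 min it fell to between −0.02 and 0.07, depending on ε. In another it ranged from 0.03 to 0.15. The sizes depend on the simulated data; the instability is the point.

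**6. Merging.** Take a second assumed day, with school 195, sleep 570, screen 150, physical activity 120, chores 45 and other 360 in term, and 0, 610, 208, 110, 60 and 452 in the holidays. Adding school to other gives 555 and 452. All four coordinates of the difference are then finite: 0.011, −0.284, 0.105 and −0.349.

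**The case against.** Three objections deserve an answer.

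**School is only an example.** The list is illustrative, the recall offers 500 activities, and an article commonly leaves grouping and zero handling to a fuller document. It is true that the absence of a zero-handling rule is not a fault here, and sporadic zeros in ordinary parts are routine detail. But the article names school as a part and also names a transformation and a contrast that cannot accept it. That is an incompatibility in what is stated.

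**Replacement would not alter the test.** A reader might infer from the table above that the Hypothesis 3 association depends on the imputed value. Step 3 shows that it does not when all children have zero and one constant is used. The 5.63-to-2.89 range is a shift in level. What survives is narrower: an uninformative holiday value, school substitutions set by the constant, and instability once zeros are mixed.

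**Most of the plan is untouched.** A reader might also infer that Hypothesis 3 as a whole cannot be computed. The documents do not support that. The accelerometry composition (sleep, sitting and three activity intensities) has no part tied to school attendance, and the worked substitution example, sitting to moderate-to-vigorous activity, is in intensity terms. Hypotheses 1 and 2, the outcomes and the sample size do not use the compositions.

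For diet, a reader might infer that the analysis fails in the same way. Zeros are plausible if food groups come from a single recall. But no groups are defined, the frequency of zeros cannot be derived from the documents, and the plan already offers the macronutrient mix as an alternative.

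**Conclusion.** The concern holds, within limits. As written, the holiday MARCA coordinates and the MARCA term-minus-holiday difference are undefined for every child with no holiday school time. The defect is confined to the MARCA arm of Hypothesis 3 and to substitutions into or out of school.

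The conclusion rests on one premise that the article does not state: children do not attend school in the summer holidays. Occasional attendance at a programme coded as school would not remove the zero for most children, and would bring in the mixed case of step 5. The numerical sizes rest on assumed minutes and are illustrations. That the logarithm of zero is undefined needs no assumption about minutes.

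This should be settled before analysis. It does not threaten the primary comparison of rates of change. The food-group point is secondary and cannot be sized.

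**What to change.** Define the MARCA parts so that each can occur in both periods. There are two ways:

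- recode time at school to the recalled behaviour (class sitting, active play, sport, transport), for which the 500-activity recall at a resolution of 5 min or more gives scope; or
- amalgamate school with a part present in both periods.

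If school time itself is of interest, analyse it separately in minutes. Do not rely on small-value replacement for this zero.

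For diet, if food groups are used, merge them until no group is zero, or use the macronutrient mix already offered.

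The cost is a change of wording and a recoding table fixed before analysis, with no new data. The downside is that school is no longer its own part of the composition. That is a real loss, since the structure of the school day is central to the article's rationale; the separate analysis in minutes recovers part of it.

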## Discussion

The focus of this study is to track changes in children’s fitness and fatness during the school year compared with the summer holidays across three successive school years, and to explore whether rates of change in these outcomes are associated with changes in diet and time use among Australian school children. There are policy implications if the holiday environment leads to increased fatness and decreased fitness. Potential interventions may target the home environment, and/or effectively extend the in-school environment. This could be achieved, for example, through use of family-based interventions, summer camps and summer school programs. Summer camps and programs offer a mix of physical and specialised learning activities and may provide the structured day needed to prevent weight gain and losses in fitness.

There is strong evidence that summer camps, with appropriate activity components, can be effective in promoting physical activity [64, 65]. While there is little research, it has also been suggested that summer camps may provide a valuable setting for interventions aimed at improving children’s diet over the summer holiday period as they provide a structured environment where camp administrators determine the food provided to children [66]. Increased summer holiday physical activity and improved diet may translate into lower fatness and higher fitness [67–69].

Family-based interventions may also provide a strategy to prevent unhealthy changes in health outcomes. Although challenging, especially during the holiday diaspora, family-based interventions can be effective in increasing physical activity, with a recent systematic review [70] showing a small-to-moderate benefit (ES = 0.29). A further systematic review found family-based interventions were more effective than school-based interventions for reducing obesity in children under the age of 12 [71].

## Conclusions

Emerging evidence suggests that the summer holiday period is characterised by increased fatness and decreased fitness. It is possible that these patterns may be due to changes in diet and/or time use (e.g. children may be less active, eat more and have more screen time during the school holidays, compared with the in-school period). However, few studies have tracked diet and time use across the holiday period. Thus, the focus of this project is to track changes in fitness, fatness, diet and time use of 9–11-year-old children across three successive years and compare rates of change between in-school and summer holiday periods. Findings from this project are likely to inform new, potent avenues for intervention efforts aimed at addressing childhood fitness and fatness.

## Data Availability

The datasets will not be publicly available due to ethical restrictions (participants have not consented to the use of their data for purposes other than those for which they originally consented). An ethically compliant dataset could be made available upon reasonable request to the corresponding author.

## Abbreviations

%BF: percentage body fat
ASA24: Automated Self-Administered 24 h Dietary Assessment Tool
AUSNUT: Australian Food Supplement and Nutrient Database
BIA: Bioelectrical Impedance Analyser
BMI: Body mass index
ICSEA: Index of Community Socio-Educational Advantage
MARCA: Multimedia Activity Recall for Children and Adults
SEP: socio-economic position
TDEE: total daily energy expenditure
